Multiple factors can contribute to the development of PICS, including metabolic and neuroendocrine processes directly related to the critical condition of these patients. However, other factors have been documented that may be at least partially induced by medical interventions, procedures, and medications implemented in the ICU, making them potentially preventable or modifiable. (2,6,7)

Swallowing disorders are common in patients with PICS, with prevalence varying in different studies depending on the chosen population, study design, and diagnostic criteria used, ranging from 3-70%. (1,8–10) It is estimated that more than one in six patients admitted in an emergency condition and at least one in ten medical-surgical patients are affected by post-extubation dysphagia. (11)

In some cases, dysphagia may resolve or significantly improve within days, while in other cases, it may persist for long periods. (12) Specifically in the postoperative context, the incidence of dysphagia has been reported to be around 18.3%, with up to 80% persisting at ICU discharge and more than 60% persisting until hospital discharge. (10) Additionally, postoperative dysphagia has been established as an independent predictor of 28- and 90-day mortality. (12) Therefore, the early use of strategies for recognizing post-extubation dysphagia and regular and periodic reevaluation in the ICU should be a standard of care. (13)

Swallowing disorders are closely associated with post-extubation aspiration events, which have been persistently linked to deleterious outcomes for patients, including increased morbidity and mortality, longer hospital and ICU stays, the need for re-intubation, and pneumonia, among others. (1)

Safe and efficient swallowing is a complex process that requires the coordination of various structures; and the execution of both cranial and spinal nerves to convert respiratory impulses into digestive ones and vice versa. It also involves structures of the upper aerodigestive tract, where the closure of the laryngeal vestibule is crucial, which must be performed in a short period, leaving very little margin for error. (1)

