### Specific Objectives:

- To describe the sociodemographic and clinical characteristics of patients with invasive mechanical ventilation in the Neurological Intensive Care Unit at Fundación Santa Fe de Bogotá.
- To evaluate the efficacy of early multimodal therapy versus late multimodal therapy in terms of ventilator-free days and other secondary outcomes.

- To establish the sociodemographic and clinical factors associated with the type of therapy (early or late) the primary outcome (ventilator-free days) and secondary outcomes.
- To evaluate the safety of early multimodal therapy versus late multimodal therapy in terms of adverse events, serious adverse events, episodes of broncho-aspiration, and healthcare-associated pneumonia.
- To evaluate the impact of different predefined subgroups, such as the type of respiratory failure (hypoxemic or hypercapnic) and the type of patient (surgical, respiratory, burn, cardiovascular), on the primary outcome results.

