## 6.7. Measurements

Within the framework of the protocol, measurements will be conducted at six key moments of the research: upon admission to the intensive care unit, during observation in the intensive care unit, at the start of ventilatory support weaning, post-extubation, upon hospital discharge, and at the end of the observation period. Additionally, continuous measurements of outcomes associated with the safety of the intervention will be performed.

Upon admission, crucial details about each patient will be collected, such as name, identifier code, medical record number, sex, and ethnicity. Health and functionality aspects will also be evaluated, including the Barthel Index and Body Mass Index. Diagnostic information will be complemented with the ICD-10 code, study group (early vs. late), and the unit of admission (surgical, neurological, septic and respiratory, cardiovascular, or burn unit). Severity scores such as SOFA, APACHE II, and SAPS II will be incorporated, along with temporal data such as admission date, discharge date, and the time elapsed from intubation to the start of therapy. Regarding respiratory parameters, fundamental variables at the time of intubation will be detailed, such as tidal volume, respiratory rate, PEEP, plateau pressure, static lung compliance, driving pressure, airway resistance, and the PaO2/FIO2 ratio.

During the observation phase, a rigorous daily patient evaluation process will be implemented to ensure accurate recording of their progress. Key variables will be monitored, such as days on mechanical ventilation (recording start and end dates), ventilator-free days, days with delirium (indicating start and end dates), days of hospitalization with delirium, and days of sedation (with details of start and end dates). The duration of mechanical ventilation, the possible need for tracheostomy, the presence of adult respiratory distress syndrome, and the eventual occurrence of healthcare-associated pneumonia will also be documented.

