| Dysphagia 72 hours after extubation                     | Dysphagia 72 hours after extubation                                               | Qualitative Nominal | Yes or no                                                                                                                                                                                                                                                                                                                                                                                                                                                                       |
| Oral start time.                                        | Time in which the oral route is started after extubation.                         | Qualitative Nominal | 
1: 12-24 hours
 
2: > 24 hours
                                                                                                                                                                                                                                                                                                                                                                                                                                   |
| Healthcare-associated pneumonia                         | The patient developed healthcare-associated pneumonia during his stay in the ICU. | Nominal qualitative | 
0 = No
 
1 = Yes
                                                                                                                                                                                                                                                                                                                                                                                                                                                    |

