|-------------------------|---------------------------------------------------------------------------------|---------------------|----------------------------------------------------------------------------------------------------------------------------------------------------|
|                         |                                                                                 |                     | 2 = Oxygen desaturation requiring medical management                                                                                               |
| Pain or agitation       | The patient experienced pain or agitation during therapy.                       | Nominal qualitative | 0 = No
1 = Pain or agitation without requiring medical management
2 = Pain or agitation requiring medical management                         |
| Invasive line removal   | The patient accidentally or unscheduled removed an invasive line during therapy | Nominal qualitative | 0 = No
1 = Yes                                                                                                                                  |
| tachypnea               | The patient presented tachypnea during therapy.                                 | Nominal qualitative | 0 = No
1=Tachypnea without the requirement for medical management
2=Tachypnea requiring medical management                                   |
| Neurological impairment | The patient presented with neurological deterioration during therapy.           | Nominal qualitative | 0 = No
1=Neurological deterioration without the requirement for medical management
2=Neurological deterioration requiring medical management |
| Unscheduled extubation  | The patient was extubated unscheduled during the ICU stay.                      | Nominal qualitative | 0 = No
1 = Yes                                                                                                                                  |

|                   |                                                           |                     |                   |
|-------------------|-----------------------------------------------------------|---------------------|-------------------|
|                   |                                                           |                     |                   |
| Bronchoaspiration | The patient aspirated bronchodilators during the ICU stay | Nominal qualitative | 0 = No
1 = Yes |

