### Procedures for Data Collection

Data will be collected by clinical staff, therapists, and research assistants from the intensive care unit, all of whom are familiar with the study and the predefined variables. The interventions and variables collected by the therapists are detailed in the Clinical Trial Operational Plan (Annex 1). Data collection will take place on the third and fourth floors of the Intensive Care Unit at FSFB. Training will be provided to all investigators on data collection and the specific times to complete the data collection instrument. Additionally, knowledge of the protocol will be assessed through an exam, which will be considered passed with a score above 4, and feedback will be provided to address any deficiencies. The variables measured by the therapists will be recorded daily from the start of the intervention. Measurements will be taken at five key points in the research: upon admission, during observation in the intensive care unit, at the start of weaning from ventilatory support, before and after extubation, and at the end of observation. Finally, a follow-up will be conducted 90 days after endotracheal intubation, during which patients or their legal representatives will be contacted by phone to assess mortality.

To ensure data quality, the following strategies will be implemented:

**Data Validation During Entry:** Verification of formats, ranges, and logical consistency of the data will be performed at the time of entry.

**Double Data Entry:** Two investigators will independently enter the same data, and then compare them to identify discrepancies. Any discrepancies found will be investigated and corrected.

**Consistency and Coherence Verification:** Checks will be carried out to ensure that the data do not present contradictory or incoherent information in the records.

**Extreme Value Checking:** Extreme or atypical values in the data will be identified and verified to ensure their validity.

**Quality Control in Later Stages:** Cross-checks will be performed, random samples of the results will be reviewed, and external validation methods will be used whenever possible.

These strategies will be implemented to ensure the quality and reliability of the data collected in the study.

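### Pneumonia and bronchoaspiration are counted only during the ICU stay, so ward events are missed in both arms and an arm that leaves the ICU sooner is watched for less time

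*Protocol*

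**What the plan says.** The variable table in Section 6.11 holds the only operational definitions of the two events, both coded yes/no. Healthcare-associated pneumonia is "The patient developed healthcare-associated pneumonia during his stay in the ICU". Bronchoaspiration is "The patient aspirated bronchodilators during the ICU stay".

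Both belong to the safety objective in Section 5, which names "adverse events, serious adverse events, episodes of broncho-aspiration, and healthcare-associated pneumonia". Pneumonia also appears among the effectiveness outcomes: as secondary in the PICOT table of Section 3 and as exploratory in Section 6.6.

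No other section sets a longer window:
- Section 6.7 promises that "continuous measurements of outcomes associated with the safety of the intervention will be performed", but gives no end date and places pneumonia recording in the ICU observation phase.
- The outcome lists in Sections 3 and 6.6 and the forms in Annexes 4 and 5 name the events without a window.
- At day 90, under Procedures for Data Collection, "patients or their legal representatives will be contacted by phone to assess mortality". Nothing else is asked.

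On the duration of risk, Section 4 reports for postoperative patients that "the incidence of dysphagia has been reported to be around 18.3" per cent, "with up to 80% persisting at ICU discharge and more than 60% persisting until hospital discharge". It adds: "Swallowing disorders are closely associated with post-extubation aspiration events", and names pneumonia among the consequences.

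**The concern.** There are two separate problems.

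The first applies whatever the treatment does. The protocol describes a risk that often continues on the ward, yet stops counting its consequences when the patient leaves the ICU. Pneumonia or aspiration on the ward goes unrecorded under these two outcomes in both arms.

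The second is conditional. ICU length of stay is a listed outcome in Section 6.6, and the trial hypothesis is shorter ventilation with early therapy. If that carries over into ICU stay, the observation window is shorter in the early arm because of treatment. Section 6.13 compares categorical variables by chi-square or Fisher tests and states no allowance for time at risk. A shorter window can then appear as fewer events. The error would favour the early arm on safety, in a field where Section 4 itself cites a 750-patient trial with more adverse and serious adverse events under early mobilisation.

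**Working it through.** The plan gives no figure of its own to reproduce. The check has three parts.

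**1. Does the risk outlast the window?** Inputs: 74 patients (Section 1), and from Section 4 an 18.3% incidence, up to 80% persisting at ICU discharge and more than 60% at hospital discharge. Assume that all 74 are extubated and that the postoperative figures apply to them.

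- With dysphagia: 74 × 0.183 = 13.5.
- Still affected at ICU discharge, as an upper figure: 13.5 × 0.80 = 10.8.
- Still affected at hospital discharge: 13.5 × 0.60 = 8.1, or 10.8 × 0.60 = 6.5 if the 60% refers only to those affected at ICU discharge.

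The input is uncertain. Section 4 also gives 3% to 70% as the range for swallowing disorders across studies; with the same 80%, that is 74 × 0.03 × 0.80 = 1.8 to 74 × 0.70 × 0.80 = 41.4 patients. These are patients at risk after the window closes, not missed events. The protocol gives no post-ICU pneumonia or aspiration rate, so missed events cannot be counted.

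**2. What can an unequal window do by itself?** Section 6.3 plans on 6.1 vs 3.4 ventilation days, a difference of 2.7. Assume that this carries into ICU stays of 8.0 days (late) and 5.3 days (early), and that the daily risk h is the same in both arms and in ICU and ward. The proportion recorded in the ICU is 1 − (1 − h)^days.

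| Assumed h per day | Late, 8.0 days | Early, 5.3 days |
|---|---|---|
| 1% | 7.7% | 5.2% |
| 2% | 14.9% | 10.2% |
| 3% | 21.6% | 14.9% |

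At 2% per day this is 37 × 0.149 = 5.5 against 37 × 0.102 = 3.8 patients, a gap of fewer than two events.

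For sensitivity, set ICU stay to the planned ventilation days plus 0, 2 or 5 days, use h from 0.5% to 3%, and compute 1 − exp(−h × days). The early/late risk ratio is then 0.56–0.58, 0.67–0.69 or 0.76–0.79. A full 28-day window under the same equal risks gives a ratio of 1.00.

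**3. Would hospital discharge do as the endpoint?** Hospital stay is also a listed outcome. With h = 2% and assumed hospital stays of 14.0 and 11.3 days (the same 2.7-day gap), 1 − 0.98^14.0 = 24.6% and 1 − 0.98^11.3 = 20.4%. The same fault returns in a milder form, so the window has to be fixed in calendar days.

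**The case against.** The intervention is given only in the ICU, so an on-treatment safety window is defensible. Section 2 says that prolonged ventilation raises the risk of ventilator-associated pneumonia. If most risk falls while the patient is ventilated, the ICU window captures most of it, and fewer pneumonias after shorter ventilation would be a real benefit, not an artefact. The same 750-patient trial found no difference in ventilation days or days out of the ICU, so the stays may not differ at all. Annex 5 records both events without an ICU restriction, serious adverse events have no stated window, and time-at-risk methods may be left to a SAP.

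Much of this stands. It limits the size of the distortion and makes the difference between arms conditional. It does not remove the truncation: the only definitions say ICU, and a form without a window does not extend them. A serious adverse event count may catch some later cases, but not as the two outcomes named in the objective. A SAP can adjust for time at risk in the ICU, but it cannot recover ward events that were never collected.

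A reader might also infer from the word bronchodilators in the table that almost no aspiration would be counted. The documents do not support that. The event is correctly named in Sections 3, 5 and 6.6 and in Annex 5, and the table has similar translation slips, such as COUCH for SOFA. It is a clerical error.

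**Conclusion.** The point holds in a limited form. As written, both events stop being counted at ICU discharge, although the protocol's own background says that the underlying swallowing problem often persists. Ward events are lost in both arms. A difference in observation time between arms arises only if ICU stay differs.

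The apparent reductions in the table rest on assumed ICU stays, assumed daily risks and equal risk in ICU and ward; none of these is in the protocol. A reader might infer that the trial will show about a third fewer pneumonias spuriously, or that some 11 cases will be missed. Neither follows. The first is one illustration, which shrinks if risk is concentrated during ventilation. The second confuses patients with dysphagia with patients who have an event, and uses an upper-bound persistence figure from postoperative patients.

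The primary endpoint is not affected, and Section 6.6 ranks pneumonia as exploratory for effectiveness. The weight of the point lies in the safety objective, where the possible error favours the early arm. The correction is cheap and worth making.

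**What to change.** In Section 6.11, define both events as occurring from randomisation to a fixed day 28 in both arms, the window already used for delirium, sedation and ventilator-free days. Flag each event as ICU or ward. Take them from hospital records, and ask about events after hospital discharge, up to day 28, at the existing day-90 call. Where follow-up ends before day 28, analyse by time at risk with death as a competing event. Do not use hospital discharge as the endpoint, since it may also differ by arm. Keep the ICU-only count as a supportive result, reported also per ICU-day. Add the window to Annexes 4 and 5 so that forms and definitions agree, and correct the wording of the bronchoaspiration definition at the same time.

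The cost is chart review for ward days and a few extra questions in a call already planned. The downside is that ward events, and still more those after discharge, will be less completely documented than ICU events; the ICU/ward flag and the supportive ICU count let a reader judge how much that matters.

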There are several moments when tongue function can be affected by mechanical ventilation. From the moment of endotracheal tube insertion with a laryngoscope that compresses and deviates the tongue during the procedure, lingual nerve injuries can occur, resulting in loss of sensation. Additionally, immobilization or reduced frequency and range of tongue movement during intubation can decrease its contractile strength. (10,15,16) It has been shown that somatosensory and motor impairment of the tongue occurs regardless of age, sex, smoking history, and patient comorbidities. Compared to a control group, the decrease in strength was more persistent than sensory alteration, which has shown at least partial improvement within 14 days post-extubation. (15)

Post-extubation dysphagia is associated with delayed resumption of oral intake, potentially increasing the risks of dehydration and malnutrition in patients who are often in hypercatabolic processes, which is particularly important in the elderly population, who are often frail and have limited functional reserve. (1,9) Other factors associated with swallowing disorders in ICU patients include gastroesophageal reflux and desynchrony between breathing and swallowing processes. (10)

Extubation failure, usually defined as the need for re-intubation within 24-72 hours following planned extubation, leads to a worse prognosis, increased mortality, and hospital stay, and can occur in 2-25% of patients. Causes include swallowing dysfunction, ineffective cough, upper airway obstruction, and excessive secretions in the airway. (17) In a related study of patients in a medical-surgical ICU, intubated for more than 6 days, it was found that the gag reflex is a determinant for extubation failure related to aspiration or excessive secretions in the airway. (17) Both frailty and generalized weakness have been associated with impaired ability to generate an effective cough to expel tracheal material. (1)

The growing concern to minimize the impact of medical interventions on the overall recovery process of patients has led to a cultural shift in ICUs, where it was previously more common to find most patients deeply sedated and on invasive mechanical ventilation, sometimes for prolonged periods, and today, fostering an increasingly conducive environment for rehabilitation. (18)

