## 6.6. Outcomes

### *Effectiveness*

Main outcome: time (days) from intubation to extubating.

- Secondary outcomes:

- Days free of mechanical ventilation until day 28
- Days of delirium until day 28
- Time in ICU with delirium until day 28
- Days of hospitalization with delirium until day 28
- Days of sedation until day 28
- Sedation-free days until day 28
- Extubating failure
- Need for non-invasive mechanical ventilation
- Exploratory outcomes:
- Barthel index at discharge
- Days of hospital stay
- Length of stay in ICU
- Mortality from any cause up to 90 days
- Time from intubation to start of therapy
- Muscular strength measured with the Medical Research Council (MRC) scale
- Dysphagia 72 hours after extubation
- Dysphonia 72 hours after extubation
- Time until initiation of oral administration post-extubation
- Development of healthcare-associated pneumonia,
- Maximum mobility measured by JH-HLM
- Grip strength
- Cognitive function measured using the Montreal Cognitive Assessment (MOCA)
- Evaluation of functionality in daily activities until day 28
- Quick sensitivity and dexterity test

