1. Oxygenation (O): The PaO2/FiO2 ratio > 150, arterial oxygen saturation > 90% with FIO2 0.4, PEEP ≤ 8 cm H2O and Tobin's index (fr/Vt) < 105. Each variable will be marked as yes or no.
2. Respiratory Mechanics (M): exhaled tidal volume greater than 5 ml/kg vital capacity > 10 ml/kg, maximum inspiratory pressure (MIP) ≤ -20 to 25 cmH2O, respiratory rate < 35 per minute, and values of PIM and PEM.
3. Acid-Base (A): paCO2 < 50 mmHg, pH > 7.32, lactic acid > 2, and venous saturation > 75%.
4. Hemodynamic (H): Systolic pressure > 90 or < 160, heart rate ≤ 140 per minute, the presence of arrhythmias and doses of vasopressors (high > 0.2 mcg (kg/min)
5. Airway (A): history of difficult airway and leak test results > 40%.
6. Clinical Component (+): Additional clinical factors, such as the presence of effective cough, management of secretions, the patient's neurological status, resolution of the underlying cause of intubation, and the manifestation of clinical signs of respiratory distress, as well were considered.

After extubation, several indicators will be carefully monitored to assess the patient's recovery and stability. The presence of dysphonia at 72 hours, maximum mobility measured by JH-HLM at 24 hours, and grip strength within the same period will be recorded. Additionally, the need for non-invasive mechanical ventilation at 48 hours will be evaluated, indicating whether it is required or not. The possible presence of dysphagia at 72 hours will also be documented, along with the timing of oral intake initiation, classified into two options: 1) between 12 and 24 hours, and 2) after 24 hours. The occurrence of extubation failure at 48 hours will be recorded, indicating whether

it occurred or not, and muscle strength will be measured using the MRC Scale at 24 hours to assess the patient's functional capacity after the extubation procedure.

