| Grip strength at the time of extubation | Grip strength of the dominant hand within 24 hours after extubation                                                                                   | Continuous Quantitative | Kilograms

It will be 0 if the patient dies. |
| Failed extubation                       | Inability to breathe spontaneously in the first 48 hours after removal of the artificial airway and the patient is unable to maintain a patent airway | Qualitative Nominal     | Yes or no                                          |
| NIV POS extubation                      | Post-extubation non-invasive ventilatory support within 48 hours                                                                                      | Qualitative Nominal     | NOT = 0

IF = 1                              |
| Prolonged mechanical ventilation        | Invasive mechanical ventilation longer than 14 days                                                                                                   | Qualitative Nominal     | Yes or no                                          |
| Tracheostomy                            | Need to use a tracheostomy tube.                                                                                                                      | Qualitative Nominal     | Yes or no                                          |
| Adult respiratory distress syndrome     | Bilateral alveolar infiltrates with a PAFI less than 300.                                                                                             | Qualitative Nominal     | Yes or no                                          |

|                              |                                                                                                                   |                     |                                                                                                                                                                                                                                                    |
|------------------------------|-------------------------------------------------------------------------------------------------------------------|---------------------|----------------------------------------------------------------------------------------------------------------------------------------------------------------------------------------------------------------------------------------------------|

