Variables that could act as confounding factors will be evaluated through a second multiple regression model. In this model, the potentially confounding variable will be removed, and the resulting slope or estimator (adjusted estimate) will be calculated. If there is a change greater than 15%-20%, the confounding variable will be included in the final model. Otherwise, the most parsimonious model will be chosen.

To evaluate the interaction between two variables, another regression model will be performed, including a new variable resulting from multiplying the two potentially interacting variables. If the regression coefficient of this new variable has a significance level of less than 0.05, it is concluded that there is an interaction, and this variable will be included in the model. Variables with potential interaction will be identified by evaluating confounding factors. Researchers will also evaluate clinical variables that may be considered as interaction or confounding variables through the above-described strategy.

The assumption of proportional hazard will be evaluated using Schoenfeld residuals, and influential values will be analyzed through residuals versus observations plots. Multicollinearity will be assessed through matrix curves.

Logistic regression models will be used to assess the relationship between our dichotomous variables, such as failed extubation, post-extubation NIV, prolonged mechanical ventilation, tracheostomy, and dysphonia, and the other studied variables. The assumptions of a logistic regression model, such as linearity in the log of the odds, independence of errors, homogeneity of variance, absence of multicollinearity, absence of outliers, and proportionality of effects, will be evaluated through residual analysis and graphical diagnostics, such as Pearson residual analysis or deviance residual analysis.

A multiplicity adjustment strategy will be employed in statistical tests, such as the Bonferroni method, Holm-Bonferroni, or other methods that control the false discovery rate (FDR), to maintain the overall type 1 error rate at an acceptable level.

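### Failed extubation is defined by two conditions joined with *and*, with no mention of reintubation, so failures of a single kind may be coded no

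*Protocol*

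**What the plan says.** For failed extubation, the variable table in section 6.11 of the Protocol holds the only operational definition: "Inability to breathe spontaneously in the first 48 hours after removal of the artificial airway and the patient is unable to maintain a patent airway". It is coded yes or no. Neither condition is given a criterion, and reintubation is not mentioned.

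Other places bear on the same outcome:

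- **Section 4 (background)** describes extubation failure as "usually defined as the need for re-intubation within 24-72 hours following planned extubation". It adds: "Causes include swallowing dysfunction, ineffective cough, upper airway obstruction, and excessive secretions in the airway". It says that failure "can occur in 2-25% of patients".
- **Section 6.6** lists "Extubating failure" among the secondary outcomes.
- **Section 6.7** says: "The occurrence of extubation failure at 48 hours will be recorded". It gives no further criterion.
- **Annex 4** lists the outcome by name only. **Annex 5** (the data collection form) has a yes/no entry at 48 hours, without a definition.
- **Section 6.13** plans logistic regression for dichotomous variables "such as failed extubation, post-extubation NIV, prolonged mechanical ventilation, tracheostomy, and dysphonia".

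**The concern.** A definition that needs both a breathing problem and an airway problem is narrower than the concept in the protocol's own background. There, the need for reintubation is the event, and breathing, airway, cough and secretion problems are possible reasons for it. Under the table's wording, a patient who returns to the ventilator for one kind of problem alone is not a failure.

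The outcome has a particular job in this trial. The main outcome in section 6.6 is time from intubation to extubation, and section 6.13 builds its Cox analysis on ventilation time and extubation yes/no. A patient extubated early and reintubated the next day can therefore count as an early success. Failed extubation is the most direct listed check on whether a shorter time reflects durable liberation from the ventilator. If its definition misses some failures, or leaves them to individual judgement, that check is weakened. Section 6.1 blinds only the day-90 evaluators and the analysts, so the staff who code this item know the allocation.

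**Working it through.** The protocol states no event count, power or sample size for this outcome, so there is no figure to reproduce. The check is on wording, followed by a range.

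**Step 1. Apply each rule to the same patients.** Take patients reintubated within 48 hours and ask how each rule codes them.

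| Patient reintubated within 48 h | 6.11 as written (both) | Either condition | Reintubation, any cause |
|---|---|---|---|
| Cannot breathe unaided, airway not patent | yes | yes | yes |
| Cannot breathe unaided, airway open (e.g. fatigue) | **no** | yes | yes |
| Airway not patent, still breathing unaided | **no** | yes | yes |
| Neither condition judged present | **no** | no | yes |

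The second row is the clear case: the written rule gives no for a patient whom section 4 would call a failure. The third row depends on whether a patient with an obstructed airway is judged able to breathe spontaneously, which the definition does not settle. Compared with an either-condition rule, the written rule can only lower the count.

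**Step 2. Look for a repair elsewhere.** Section 6.7 and Annex 5 ask for yes or no at 48 hours, and Annex 4 gives the name alone. None of the variables in 6.11 and none of the Annex 5 fields records reintubation or its cause. The outcome therefore cannot be rebuilt from the form under a different definition. Because the form carries no definition, staff might equally mark every reintubated patient yes, or mark yes for a patient managed on non-invasive ventilation and never reintubated. Error can run in either direction.

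**Step 3. Bound the possible undercount under the literal rule.** The inputs are 74 patients (section 1), a failure rate of 2-25% (section 4), and *f*, the share of failures that meet both conditions. The documents do not give *f*, so it is an assumption ranging from 0 to 1. All 74 patients are assumed to be extubated.

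True failures = 74 × rate: 74 × 0.02 = 1.48 and 74 × 0.25 = 18.5.

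Counted failures = 74 × rate × *f*; share lost = 1 − *f*.

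| *f* | Counted at 2% | Counted at 25% | Share lost |
|---|---|---|---|
| 1 | 1.48 | 18.5 | 0% |
| 0.75 | 1.11 | 13.9 | 25% |
| 0.5 | 0.74 | 9.3 | 50% |
| 0.25 | 0.37 | 4.6 | 75% |
| 0 | 0 | 0 | 100% |

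The share lost is simply one minus the assumed *f*, so the documents support no point estimate.

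**The case against.** The strongest reply is that too much is being read into one connective. The English of the variable table is visibly loose: the SOFA acronym is rendered as a piece of furniture, and bronchoaspiration is described as aspirating bronchodilators. The word *and* may only list two forms of failure. A patient with an obstructed airway may also be judged unable to breathe spontaneously, so the two conditions could overlap heavily. Section 4 is a literature description with a 24-72 hour window and is limited to planned extubation, so differing from it is weaker than contradicting an operational rule. Other signals are collected as well: non-invasive ventilation within 48 hours, tracheostomy, prolonged ventilation and unscheduled extubation. The same rule applies to both arms, and no differential bias is shown.

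Much of this stands, and it limits the point. A reader might infer that most reintubations would be coded no. Assuming, for example, that 10-30% of failures meet both conditions gives a loss of 70-90%. The documents do not support that: they give no split of failures by mechanism and no overlap, and the causes in section 4 are not said to be mutually exclusive. Nor does sparse data in the logistic regression arise mainly from this wording, since even a complete count could be as low as 1.48 events.

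The reply does not remove the defect. Even if *or* was meant, two raters can follow the text and code the same fatigued patient differently. The other recorded signals do not identify reintubation.

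**Conclusion.** The point holds as a defect in the definition of a secondary outcome. Followed as written, section 6.11 codes no for a patient reintubated within 48 hours for a breathing problem with an open airway, contrary to the reintubation-based description in section 4, and nothing else in the protocol corrects this. The outcome may be undercounted, or classified inconsistently by unblinded staff.

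Confidence is high that the wording is defective and low about the consequence. The possible loss runs from 0% to 100% of an expected 1.5 to 18.5 failures, assuming the section 4 rates apply and all 74 patients are extubated. A demonstrated undercount, or a bias between arms, would be a stronger conclusion than the documents allow. The primary outcome's sample size is untouched.

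**What to change.** In section 6.11, define failed extubation as reintubation for any cause within 48 hours of extubation, keeping the plan's own window. Print the same definition beside the yes/no entry in Annex 5, so that the recorded answer is an observable event.

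If the sponsor prefers to keep the two clinical conditions, the minimum change is to replace *and* with *or*. That still leaves both conditions without criteria, and it would not capture a reintubation for some other reason.

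Two additions are optional: a field for the cause of reintubation, and a statement of how death within 48 hours without reintubation is handled.

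The cost is one changed definition and one line on the form. The reported failure rate may come out higher than under the present wording.
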